### Outcomes Measures

The primary outcome, hs-CRP, and secondary outcome the SAQ will be assessed at baseline, 7 ± 3 days and 14 ± 3 days. At all visit windows, other indicators including creatine kinase (CK), creatine kinase-myocardial band (CK-MB), cardiac troponins I (cTnI), 12-lead electrocardiograph and the syndrome scores of Qi deficiency and blood stasis will be tested and metagenomic sequencing for intestinal flora will be performed (25). Echocardiography and safety assessment will be performed at baseline and 14 ± 3 days. All adverse events will be tracked throughout the study. Table 1 lists the items measured as well as the data collection window.

**Table 1 T1:** Data collection items and measurement points.

	**Screening**	**Treatment period**		
	**(Visit 0)**	**D1** **(Visit 1)**	**D7 ± 3** **(Visit 2)**	**D14 ±3** **(Visit 3)**

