## Introduction

Non-ST-segment elevation acute coronary syndrome (NSTEACS) is the most common type of acute coronary syndrome (ACS) (1, 2). Despite proven benefits of leading-edge ACS salvage strategies, NSTEACS has a high 1-year main adverse cardiovascular and cerebrovascular events (MACCE) rate of 8.7%, and is associated with a higher risk of long-term mortality (3–5). Thus, it is vital to improve the secondary prevention of NSTEACS and reduce the incidence of MACCE.

High-sensitivity C-reactive protein (hs-CRP) is regarded as an important indicator of the incidence of MACCE. Systemic vascular inflammation plays multiple roles in the presentation of ACS, and hs-CRP is positively associated with the incidence of future MACCE (6–8). The Seattle Angina Questionnaire (SAQ) is widely utilized in the assessment of angina symptoms. The cTnI is an important biomarker to indicate the progression of acute myocardial ischemia. In addition, the disturbed intestinal flora is implicated in forming atherosclerotic plaques (9, 10). The alterations in the intestinal flora are correlated with coronary artery disease (CAD) severity via the mediation of intestinal flora serum metabolites (11). The level of trimethylamine-N-oxide (TMAO) in NSTEACS patients is significantly higher than that in healthy people and is positively correlated with the risk of MACCE (11, 12). Most studies focus on Chinese herbal compounds that act directly on target cells or organs (13). Emerging evidence indicates that Chinese herbal ingredients cannot be absorbed into the blood circulation directly through digestion (14–16). Therefore, the intestinal flora might be an important pathway for Chinese herbs to function.

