### Inclusion Criteria

Subjects who meet all of the following criteria are eligible to participate in the study: (1) diagnosed as unstable angina (UA) or non-ST segment elevated myocardial infarction (NSTEMI) according to the 2015 ESC guidelines for the management of NSTEACS (22); (2) diagnosed as the TCM syndrome of Qi deficiency and blood stasis according to the Guiding Principles For Clinical Research Of New Chinese Medicines (23); (3) age 40–60 years; (4) heart function is Killip grade I-II for subjects diagnosed as NSTEMI; (5) in-hospital patients; (6) written informed consent is obtained.

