### Randomization and Blinding

The randomization will be conducted by the Institute of Clinical Pharmacology of Xiyuan Hospital, China Academy of Chinese Medical Sciences. The SAS software-generated random sequencing in blocks of four was used for randomization. Eligible patients are randomized into the SQSX or control group on a 1:1 basis. Researchers and outcome evaluators involved in this study know nothing about the details of the randomization sequence. All patients and physicians will be unaware of treatment allocation until the end of the study. Urgent letters revealing group and treatment allocation have been prepared. If an emergency occurs, blind breaking and urgent measures may need.

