### Sample Size Calculation

The sample size was estimated using hs-CRP. Currently, the hs-CRP of NSTEACS decreased from 5.30 mg/L to 3.74 mg/L after 14 days of conventional treatment, with a decline rate of 29.43% (26). The hypothesis is that the treatment group could reduce the hs-CRP of NSTEACS by 35%. With a type I error rate of α = 0.05 and a power of 80% (a type II error rate of β = 0.2), one arm requires a sample size of 27. With a 20% drop-out rate, we have to recruit a total of 66 patients. The following is the formula for calculating sample size (27):

$$\begin{array}{l} \text{n}=2{\left[\frac{\left({\text{u}}_{\alpha }+{\text{u}}_{\beta }\right)}{\delta /\sigma }\right]}^{2}+\frac{1}{4}u_{\alpha }^{2} \end{array}$$

n, is the sample size required in each group, δ = μ_1_-μ_2_, is the difference between means of two groups, σ, is the standard deviation, u_α_ and u_β_ are the values of u corresponding to the test level α and type II error probability β, respectively.

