### Statistical Analyses

An independent biostatistician will perform statistical analysis. The result of recruitment, the specific reasons for data missing and the distribution of each statistical analysis data set will be described. The primary outcome, the change values of hs-CRP from recruitment to day 7 ± 3, day 14 ± 3 and the day of revascularization, and the secondary outcome, the change scores in five dimensions of SAQ at the same time, are both continuous variables. For comparison between groups, the continuous variables will be described using means ± SD, median, interquartile range, etc., and the Shapiro-Wilk normality test and Levene test for variance homogeneity will be performed. A Student *t* test will be used to compare two groups that have a normal distribution with homogeneous variance, otherwise the Wilcoxon rank-sum test will be used. When some continuous variables are converted into categorical variables, these categorical variables will be described using rates, and the chi-square test or Fisher's exact probability method will be used. For comparison within groups, the paired *t* test or Wilcoxon signed-rank test will be used for continuous variables and the McNemar test for categorical variables. If there are baseline imbalances, Cox regression analysis, logistic regression and multivariate analysis of covariance will be used to adjust confounding variables. The longitudinal data with repeated measures will be analyzed using the linear mixed-effects model to assess associations. The safety analysis will tabulate a detailed description of the adverse reactions, adverse events and serious adverse events and compare the difference in incidence between two groups using Fisher's exact probability method. A difference of *P* < 0.05 at two-tailed test will be considered statistically significant in all analyses. The statistical analyses will be performed using SAS software version 9.4 (SAS Institute, Cary, NC, USA).

After metagenomic sequencing is completed, microbiota community structures will be compared at different taxonomic levels. The abundance and diversity of intestinal flora will be analyzed. The relationship between microbiota composition and clinical outcomes will be investigated using univariate and multivariate linear and nonlinear mixed and regression models. Gene annotation will be conducted to study the function of the intestinal flora.

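### cTnI, CK and CK-MB are compared across a mixed UA and NSTEMI sample with no routine adjustment for baseline level or diagnosis, which costs precision without biasing the test

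*Protocol article*

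**What the plan says.** All references are to the protocol article.

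- **Population (Inclusion Criteria).** Both diagnoses enter one trial: "diagnosed as unstable angina (UA) or non-ST segment elevated myocardial infarction (NSTEMI) according to the 2015 ESC guidelines".
- **Allocation (Randomization and Blinding).** "The SAS software-generated random sequencing in blocks of four was used for randomization", and "Eligible patients are randomized into the SQSX or control group on a 1:1 basis". No stratification by diagnosis is stated.
- **Markers (Outcomes Measures and Table 1).** "At all visit windows, other indicators including creatine kinase (CK), creatine kinase-myocardial band (CK-MB), cardiac troponins I (cTnI" are measured at baseline, day 7 ± 3 and day 14 ± 3. Table 1 lists them under outcomes and adds a screening value. They are neither the primary outcome (hs-CRP) nor the named secondary outcome (SAQ).
- **Purpose (Introduction).** "The cTnI is an important biomarker to indicate the progression of acute myocardial ischemia".
- **Analysis (Statistical Analyses).** Continuous variables are compared between arms by a Student t test if normality and equal variance hold; "otherwise the Wilcoxon rank-sum test will be used". Covariance adjustment is conditional on baseline imbalance. A linear mixed model is planned for repeated measures, with no covariates named. The two-sided 0.05 threshold applies to every analysis. Change from baseline is defined for hs-CRP and SAQ only; for the markers the section does not say whether levels or changes are compared.
- **Sizing (Sample Size Calculation).** "The sample size was estimated using hs-CRP". No power is claimed for the markers.

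**The concern.** The two diagnoses may differ widely in necrosis-marker level at entry. If they do, an unadjusted comparison of the pooled sample leaves that difference, and each patient's own starting level, in the error term. Baseline values are already collected and would remove much of this spread. Adjusting only after an imbalance has been noticed, with no criterion and no named covariates, does not secure that gain.

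A second risk depends on two conditions that the document does not state. Suppose raw change were the quantity compared, and marker levels had largely fallen by follow-up in both arms. Change would then be close to minus the baseline value. If one arm happened to hold more NSTEMI patients, it would show a larger fall in troponin whatever the treatment did, and a reader could take that for a drug effect.

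**Working it through.** **What can be reproduced.** There is no marker calculation to reproduce. The 27 per arm was derived for hs-CRP and is used here only as the arm size. It cannot be reproduced either, because σ has no stated value. With δ = 3.74 − 0.65 × 5.30 = 0.295 mg/L, the printed formula returns 27 (two-sided) only if δ/σ ≈ 0.78, so σ ≈ 0.38 mg/L. For the total, 27 × 1.2 = 32.4, so 33 per arm and 66.

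**Detectable effect.** With 27 per arm, two-sided 5% and 80% power, the detectable difference is (1.96 + 0.84) × √(2/27) ≈ 0.76 SD. Anything that widens the SD raises the detectable effect in proportion.

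**Illustration 1: log scale, part of the elevation remains.** Every marker input is an assumption: NSTEMI minus UA gap at baseline 3.0 log units; SD within diagnosis 0.7; correlation of baseline with follow-up within diagnosis 0.6; 30% or 60% of the gap left at follow-up (r); NSTEMI share p of 20% or 50%.

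- SD of the follow-up value = √[0.7² + p(1−p)(3.0r)²]
- SD of the log change = √[0.7² × 2(1−0.6) + p(1−p)(3.0(1−r))²]
- SD after adjustment for baseline and diagnosis = 0.7 × √(1−0.6²) = 0.56

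| r | p | SD, follow-up | SD, log change | SD, adjusted |
|---|---|---|---|---|
| 0.3 | 0.2 | 0.79 | 1.05 | 0.56 |
| 0.3 | 0.5 | 0.83 | 1.22 | 0.56 |
| 0.6 | 0.2 | 1.00 | 0.79 | 0.56 |
| 0.6 | 0.5 | 1.14 | 0.87 | 0.56 |

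Multiplying by 0.76 and exponentiating, the detectable reduction in all patients is about 1.8- to 2.5-fold unadjusted and about 1.5-fold adjusted.

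Simulated rejection rates in the same model (1500 runs per setting, true reduction 1.5-fold or 2-fold):

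| Effect | Wilcoxon, follow-up value or log change | ANCOVA on baseline and diagnosis |
|---|---|---|
| None | 3-5% | 4-6% |
| In all patients | 23-88% | 71-99% |
| In NSTEMI only | 4-34% | 7-55% |

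**Illustration 2: markers largely cleared.** Again all assumed: NSTEMI share 30% or 50%; NSTEMI baseline median 30 times the floor (log SD 1.2); residual above the floor at follow-up 5% or 20% of baseline; treatment halves that residual; UA patients stay at the floor. Ranges span repeated runs:

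| Analysis | Power |
|---|---|
| Wilcoxon on pooled raw change or level | 4-10% |
| Pooled log model with baseline and diagnosis | 13-73% |
| NSTEMI-only log ANCOVA | 37-85% |

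The correlation of raw change with baseline was −0.99 to −1.00, and the type I error about 5%.

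**Chance imbalance.** Treating each arm's NSTEMI count as binomial, the probability that two arms of 33 differ by five or more NSTEMI patients is 16% at a 20% share and 27% at a 50% share. For arms of 27 with shares of 30% and 50% it is about 18-22%. With no drug effect in Illustration 2, the raw-change test rejected in 17-20% of those imbalanced trials. Averaged over all trials it still rejects in about 5%.

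**The case against.** The strongest reply has four parts.

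1. **The document does not fix a raw change score for the markers.** This stands. The mirror-of-baseline argument is therefore conditional and cannot be described as what is planned.
2. **Randomization balances infarct status in expectation.** This stands too. A reader might infer that the tests mainly compare infarct size at baseline, or that an imbalance makes them invalid. The 3-6% rejection rate under no effect rules that out; the raised rate in imbalanced trials is part of the nominal 5%.
3. **The plan already provides covariance adjustment and a mixed model.** This stands in part. The first depends on an imbalance being seen, with no criterion, and the second names no covariates. Neither secures the precision gain.
4. **These are supporting indicators with no power claim, and their details may sit in a fuller plan.** This limits the weight of the point. It does not remove it, because the article itself states the default test, the conditional adjustment and the 0.05 threshold for all analyses.

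A reader might also infer that the comparisons have almost no power. The documents do not support that as a general statement. It needs assumed marker clearance, an assumed NSTEMI share and an effect confined to NSTEMI. If the drug acts in all patients, unadjusted power ranged from 23% to 88%. Nor does any section state that UA patients remain at the floor, or how fast the markers fall.

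**Conclusion.** The point holds as one of precision, not bias. UA and NSTEMI are pooled, no stratification is stated, and the default marker comparison ignores baseline level and diagnosis unless an imbalance prompts adjustment. Under the assumptions of Illustration 1, routine adjustment lowers the detectable reduction from about 1.8- to 2.5-fold to about 1.5-fold. Under those of Illustration 2, pooled raw comparisons have little power (4-10%) and adjusted log analyses do clearly better. No single figure can be drawn from the document, because it gives no marker variance, effect size or NSTEMI share. The misreading of raw change as a drug effect is a risk only if raw change is used and the markers have largely cleared. The weight is moderate: these are supporting outcomes, but the remedy uses data already collected.

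**What to change.** In Statistical Analyses, replace the imbalance-triggered adjustment for cTnI, CK and CK-MB with one prespecified analysis in all patients: log follow-up value adjusted for log baseline value and diagnosis (UA or NSTEMI). Adding both as covariates in the planned mixed model would do this. In addition:

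- show the NSTEMI-only result as a supportive analysis;
- report by arm the number of patients with a new marker rise after baseline;
- state that no efficacy conclusion will be drawn from pooled raw change scores.

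The cost is analysis wording only, with no new visits or samples. Trial Status reports that nothing had been analysed when the article was written, so a change made before any analysis cannot be read as driven by the data. Restricting to NSTEMI is a trade-off: it can be the more sensitive analysis if the effect lies there, but it rests on a small subset and its result cannot be claimed for UA.

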**Patients**				
Inclusion/exclusion criteria		×		
Informed consent	×			
General information ^a)^	×			
Medical and treatment history recording	×			
Randomization and allocation	×			
**Intervention**				
SQSX group				
Control group				
**Outcomes**				
hs-CRP		×	×	×
SAQ		×	×	×
Syndrome scores of Qi deficiency and blood stasis (25)		×	×	×
cTnI	×	×	×	×
CK	×	×	×	×
CK-MB	×	×	×	×
Fecal collection and metagenomic sequencing		×	×	×
12-lead electrocardiograph	×	×	×	×
Echocardiography		×		×
Safety indicators ^b)^		×		×
**Others**				
Adverse events			×	×
Drug distribution		×	×	
Medicine recycling			×	×

a) *General information includes: name, birth, sex, nationality, marriage and work, etc*.

b) *Safety indicators include: complete blood count, liver and kidney function tests, routine urine and stool tests*.

### Adverse Events

Negative or unintended clinical medical effects that occur after treatment are known as AEs, which can be manifested as symptoms, signs, and abnormal clinical or laboratory findings. During the study, all related AEs details will be documented on the CRF. UA/NSTEMI is an urgent condition. Several complications including STEMI, heart failure, malignant arrhythmia and even sudden cardiac death may occur. Therefore, first aid measures will be available under guidelines and standards to ensure the safety of patients.

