**Methods/Design:**

The study is a randomized, double-blinded and placebo-controlled trial. A total of 66 participants will be randomly allocated to one of the following two groups. Participants in the SQSX group will receive conventional treatment plus SQSX, while the placebo group will receive conventional treatment plus placebo, both for 14 days. The primary outcome, hs-CRP, and secondary outcome the Seattle Angina Questionnaire (SAQ) will be assessed at baseline, 7 ± 3 days and 14 ± 3 days. At all visit windows, other indicators including creatine kinase (CK), creatine kinase-myocardial band (CK-MB), cardiac troponins I (cTnI), 12-lead electrocardiograph and the syndrome scores of Qi deficiency and blood stasis will be tested and metagenomic sequencing for intestinal flora will be performed. Echocardiography and safety assessment will be performed at baseline and 14 ± 3 days. Adverse events will be monitored during the trial.

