### Data Management and Monitoring

All participant data on the CRF will be input into the clinical trial data management system. To ensure the authenticity, accuracy and completeness of data, several effective procedures are used. First, data cleaning will consider missing data, questionable values and inconsistent dates. After that, the source data will be verified by the supervisor to check for consistency. Third, manual checks. Clinical monitors will be appointed by the quality assurance department of Xiyuan Hospital, China Academy of Chinese Medical Sciences to undertake regular monitoring visits on the trial's progress and completion.

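### Read literally, the Adverse Events section puts only related events on the CRF, which conflicts with the all-adverse-event tracking and comparison promised elsewhere; the wording is ambiguous and should be reconciled.

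*Protocol article*

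**What the plan says.** Five places in the protocol article bear on which adverse events are recorded and analysed.

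- **Adverse Events, definition:** "Negative or unintended clinical medical effects that occur after treatment are known as AEs". Timing after treatment is the condition; no causal judgement is asked for.
- **Adverse Events, recording:** "During the study, all related AEs details will be documented on the CRF". This is the only sentence that says which events go on the CRF.
- **Abstract and Outcomes Measures:** "Adverse events will be monitored during the trial" and "All adverse events will be tracked throughout the study". Table 1 schedules adverse events at Visits 2 and 3 without qualification.
- **Statistical Analyses:** "The safety analysis will tabulate a detailed description of the adverse reactions, adverse events and serious adverse events". The plan will also "compare the difference in incidence between two groups using Fisher's exact probability method".
- **Data Management and Monitoring:** "All participant data on the CRF will be input into the clinical trial data management system". No other route into the database is described.

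The article gives no criterion, scale or assessor for relatedness, and no expected event rates.

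**The concern.** In safety reporting, a related adverse event ordinarily means one judged to be caused by the study treatment. On that meaning the recording sentence is narrower than the sections on outcomes and analysis. The analysis treats adverse events and adverse reactions as different things, and that distinction needs unrelated events in the database.

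What is at stake is the safety comparison, and safety is a stated aim of the trial. Patients have acute coronary disease and the conventional treatment includes aspirin, ticagrelor and enoxaparin. A cardiac event is readily put down to the disease, and a bleed to the background drugs. A randomised comparison of all events does not depend on such case-by-case attribution; a comparison of related events does. An analysis plan cannot repair this later, because events that were never recorded cannot be recovered at analysis.

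**Working it through.** **1. The passages side by side.** No figure in the article is in question, so the check is first one of text.

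| Step | Section | Events covered |
|---|---|---|
| Definition | Adverse Events | All, by timing |
| Monitoring | Abstract, Outcomes Measures, Table 1 | All |
| CRF entry | Adverse Events | Related (literal reading) |
| Database | Data Management and Monitoring | Whatever is on the CRF |
| Analysis | Statistical Analyses | Adverse reactions, adverse events and serious adverse events |

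The third row is the only narrow one, but everything below it depends on it. Under the literal reading, the database holds related events only. Adverse events then equal adverse reactions, serious events are limited to related ones, and the all-event Fisher comparison has no data. Under the wide reading, all five rows agree.

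**2. Size if the literal reading were applied (illustration only).** The event rates and the recorded share below are assumptions.

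- Participants per arm: 66 / 2 = 33 (total and 1:1 ratio from the article), ignoring dropout.
- True proportions with at least one event: p1 and p2 (assumed).
- Share s of those participants who have an event recorded as related, taken as equal in both arms. Recorded proportions are s × p1 and s × p2.
- Power: the sum, over all pairs (a, b) with two-sided Fisher p < 0.05, of Bin(a; 33, s × p1) × Bin(b; 33, s × p2).

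| Assumed true rates | s | Expected participants recorded, of 33 | Power |
|---|---|---|---|
| 20% v 45% | 1 | 6.6 v 14.9 | 49% |
| 20% v 45% | 0.75 | 5.0 v 11.1 | 32% |
| 20% v 45% | 0.50 | 3.3 v 7.4 | 18% |
| 20% v 45% | 0.25 | 1.7 v 3.7 | 4% |
| 15% v 30% | 1 | 5.0 v 9.9 | 21% |
| 15% v 30% | 0.50 | 2.5 v 5.0 | 7% |

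The expected counts are 33 × s × p; for example, 33 × 0.50 × 0.45 = 7.4.

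**3. Direction of the effect.** With the same s in both arms, the ratio of the recorded proportions is unchanged: (s × p2) / (s × p1) = p2 / p1. Counts, absolute difference and power all shrink. A between-arm bias would need s to differ by arm. The Randomization and Blinding section keeps patients and physicians unaware of allocation, so no such difference is expected while the blind holds.

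**The case against.** The strongest reply is that no related-only rule exists. The recording sentence does not contain the word *only*. Its grammar is loose, and it can be read as all relevant details of adverse events. The definition just before it has no causality condition. Outcomes Measures, the abstract and Table 1 all speak of adverse events without limit, and separate tabulation of reactions and events makes sense only if unrelated events are kept. A real filter would need a relatedness criterion, and the article gives none.

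This stands as evidence of intent. A reader might infer that the trial records only related events and that its safety comparison will rest on events selected by investigators. The documents do not support that as an established fact: it is one reading of an ambiguous phrase, and the weight of the other text is against it. A reader might also infer that any excess on SQSX would be missed. That too goes further than the text. Cardiac enzymes and ECG are scheduled at every visit, and blood count, liver, kidney, urine and stool tests at baseline and day 14, whatever the attribution. Some signals would therefore still be captured.

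It is also fair to say that the trial is too small to detect moderate differences even with full recording: at 15% versus 30% power is only about 21%, and an observed 5 versus 10 of 33 gives Fisher p = 0.24. So the illustration shows how a weak comparison becomes weaker, not how a sound one fails.

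What the reply does not remove is the sentence itself. As printed, *related* qualifies the events, and two staff members could apply it differently. Condensation for a journal does not explain it, because the sentence is present and conflicts with others.

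**Conclusion.** The point holds as an internal inconsistency of wording with a conditional consequence. Read literally, the CRF rule is narrower than the tracking and analysis rules; the rest of the article suggests that all events are intended. If the literal reading were applied at the site, the database would lack the events needed for the all-event comparison, and two of the three planned safety categories would become one. The main expected harm is then lost events and lost power, on the assumption that the blind holds and attribution is similar in both arms.

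The size cannot be taken from the documents. Under the assumed rates, recording half of the affected participants lowers power from about 49% to 18% (20% v 45%) or from about 21% to 7% (15% v 30%). These figures show the direction and rough scale only. The correction is worth making because it is specific and nearly free, and because an unrecorded event cannot be restored.

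**What to change.** Reconcile the Adverse Events section with Outcomes Measures and Statistical Analyses by deleting *related* from the recording sentence, and state that every adverse event and serious adverse event is entered on the CRF regardless of causality. Note relatedness separately for each event, since the planned tabulation of adverse reactions needs it. Run the Fisher comparison on all adverse events.

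If the CRF and site instructions already work this way, only the sentence changes. If they do not, correct them now: the Trial Status section reports 20 participants with completed follow-up, so up to 66 − 20 = 46 could still be covered in full. For those already completed, check source records for events left off the CRF.

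The cost is one word, a line of CRF guidance and slightly more recording in a 14-day trial of 66 participants. Sample size, blinding and treatment are unaffected.
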